## Abstract

This article describes the development of the “Time to Change Your Behavior” (TTCYB) study protocol, a theory-based, tailored print message intervention to improve compliance with the self-care regimen in patients with cardiovascular diseases. A design with a baseline measurement and two follow-ups at six and 12 months will be applied. At baseline and the six-month follow-up, patients will complete self-report questionnaires evaluating lifestyle habits and socio-demographic and psychological variables; at the 12-month follow-up, patients will answer a telephone interview assessing lifestyle habits. After the baseline measurement, patients will be randomized into one of three groups: (1) the tailored group, which will receive tailored health brochures; (2) the “non-tailored” group, which will receive non-tailored health brochures; or (3) the usual care group, which will receive no print information materials. The effectiveness of the intervention will be assessed through patients’ judgments of the brochures and changes in lifestyle. The role of socio-demographic and psychological variables as potential moderators of the materials’ effectiveness will be explored. If the TTCYB is efficacious, it will have implications for the design and implementation of tailored communication programs. Concepts from this study can be potentially extended to primary prevention among high-risk groups.

## 1. Introduction

Mortality statistics show that cardiovascular diseases (CVDs) are the most common causes of death in Europe, accounting for 45% of all deaths. More than four million people die from CVDs across Europe every year, with 1.4 million of these deaths before the age of 75 [1]. Several guidelines for the detection and management of CVDs consider lifestyle behavior change a best practice for avoiding poor outcomes related to disease severity and concurrent comorbid risk factors [2,3,4,5,6], but patients often fail to change their unhealthy habits [7,8,9]. Education about lifestyle change is a priority for patients’ health [10], and strategically designed and delivered health communication interventions offer promising strategies for promoting healthier behaviors. One of the most challenging issues in health promotion research is the creation and delivery of messages that are relevant, interesting, informative, and persuasive. Tailored print communication based on the needs, preferences, and personal characteristics of the target is an example of a communication approach that has attempted to address these characteristics and has been widely applied in the area of health promotion [11,12,13]. Tailored messages are thought to facilitate changes in several behaviors by providing personally relevant information and feedback [11]. Meta-analyses and narrative reviews have concluded that tailored messages are more effective than non-tailored ones in changing health behavior in multiple domains [13,14,15,16,17,18,19,20], including medication adherence [21], physical activity [22], and diet [23,24], all key aspects for the management of cardiovascular diseases. To date, little is known about the efficacy and the long-term outcomes of tailored versus non-tailored communication interventions: a large majority of studies on tailored interventions focused on short-term effects of tailored messages while few studies investigated long-term effects (most of them analyzed results up to six months after the intervention). Mobile technology is changing this perspective because the use of technology makes longitudinal studies more practically feasible, even if some subjects’ characteristics (e.g., age, digital skills, web accessibility) can limit their realization [14,25]. The importance of a healthy lifestyle for positive health outcomes coupled with the low reported rate of correct behaviors by cardiovascular patients prompts research to define communication strategies to improve adherence in this population. Much research is needed to determine the degree of the effectiveness of tailored communication interventions among cardiovascular patients.

### The “Time to Change Your Behavior” (TTCYB) Intervention

The “Time to Change Your Behavior” (TTCYB) is a randomized controlled intervention that uses tailored health print educational material to improve healthy lifestyle behaviors (dietary behavior, physical activity, alcohol intake and smoking behavior) in patients affected by acute coronary syndrome (ACS) or essential hypertension. It is a pragmatic intervention that primes the patient to self-manage by making relevant changes in the following four behaviors: diet, physical activity, alcohol intake, and smoking. The purpose of this paper is to outline the rationale and design of the TTCYB Intervention Study. This study will provide insight into the effect of tailored print educational materials in promoting lifestyle changes among patients diagnosed with CVDs. The specific aims of the study will be
to determine whether tailored materials are perceived as more useful, understandable, and complete compared to non-tailored ones;to understand whether the TTCYB intervention is effective in promoting changes in diet, alcohol intake, physical activity, and smoking behavior among patients with CVDs;to explore the effects of the TTCYB intervention compared with two control groups (described below) on secondary endpoints, including body mass index and systolic and diastolic blood pressure;to evaluate socio-demographic and psychological factors such as self-efficacy, locus of control, and anxiety and depression, which could moderate the effectiveness of the intervention.

The choice to develop an intervention using health print educational material comes from different reasons. Given the global scale of CVDs, preventive interventions that can reach large populations at low cost are needed. Mobile app or computer-delivered interventions have become increasingly popular in the last decade. However, tailored interventions delivered on the Web or smartphones can be especially challenging among specifics segments of the population, like older adults. Moreover, data on internet use show that a digital divide still exists around the world and Italy lags behind other European countries. A recent study has compared general social media use in the United Kingdom, Germany, the Netherlands, and Italy, showing that the latter makes the least use of them, with 40% (37 million) of the Italian population active [26]. Moreover, patients affected by acute coronary syndrome and hypertension seemed to prefer and considered more relevant print health material given by physicians compared to the internet [27]. Thus, because offering interventions on the Web or through mobile applications may exclude a vulnerable group, we preferred to use health print educational material. 

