### 2.9. Planned Statistical Analysis

Demographic data (e.g., age, gender) will be described for the total group and the subgroups separately. Continuous variables will be denoted with means, standard deviations, and medians. Categorical variables will be denoted in numbers and percentages. Group differences in behavior and physiological (BMI and blood pressure value) changes will be tested with a repeated-measures ANOVA and logistic and linear regression as appropriate, using the baseline values of these endpoints as covariates. Regressions will also be used to test for interactions of type of material with factors such as self, efficacy, locus of control, age, gender. This strategy will allow us to test whether the intervention works better in specific groups over others. Concerning patients’ judgments of the material, a *t*-test analysis and a Cross-table with chi-square statistic will be performed. All analyses will be conducted using the Statistical Package for the Social Sciences (SPSS) version 24.0 for Windows (SPSS Inc., Chicago, IL, USA) and MPlus software Version 7.0 (Muthén & Muthén, Los Angeles, CA, USA).

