## 3. Discussion

This report describes the rationale, design, and methods of the TTCYB study, a randomized controlled intervention that evaluates the efficacy of a tailored print intervention to improve healthy lifestyle in four behaviors (diet, physical activity, alcohol intake, and smoking behavior). This intervention targets a vulnerable and rapidly expanding segment of the population, CVD patients. The efficacy of the intervention in the tailored group compared to the non-tailored and usual care groups will be evaluated through patients’ judgments about the materials; changes in each one of the four lifestyle behaviors considered; improvements in body mass index, systolic and diastolic blood pressure; and medication adherence. If the TTCYB is efficacious, it will have implications for the design and implementation of tailored communication programs that aim at stimulating healthy behaviors to prevent worsening in patients with chronic diseases. The anticipated strengths of the study protocol include the target population, the longitudinal design, and the analysis not only of the intervention’s efficacy but also of the possible moderators of this efficacy. Besides, the intervention suggested in this protocol uses longitudinal tailoring based on models of health behavior combined in a way that has not been tested before to the best of our knowledge. The duration of the follow-up is one year, so it will be possible to investigate the long-term effects of the intervention. This project addresses major health issues and aims to contribute to the empirical and theoretical basis for developing effective primary and secondary preventive interventions. The proposed methodology can also be applied to other health problems that can benefit from lifestyle interventions. Finally, concepts from this study can potentially be extended to the primary prevention of cardiovascular diseases among high-risk groups.

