Actor	Maintenance and Recovery Self-Efficacy	*Do not worry if your partner and/or your family would not change their eating habits with you. It is not necessary that everyone in the family changes habits. Probably when they will see the positive outcomes that you will achieve with your diet, they will ask you for advice and suggestion to eat like you!*

**Table 3 ijerph-17-02919-t003:** Telephone survey to collect patients’ judgments after the delivery of the material.

Questions on a Five-Point Likert Scale (1 = not at All; 2 = Few; 3 = on Average; 4 = Sufficiently; 5 = Very	Dichotomous Question (Yes/No)
The material was attractive?	Have you read the material?
The material was easy to understand?	Have you stored the material?
The material encouraged your reflection?	Have you shown the material to others?
The material increased your knowledge about hypertension?	Would you read the material again in the future?
The material was personalized on your specific situation?	Was the information in the material new?
The material contained information pertinent to your specific situation?	Do you think it would be useful to receive this kind of material again in the future?
The material was complete?	
Would you make behavioral changes based on the material (specific for diet, physical activity, alcohol intake, and smoking behavior)?

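### Aim 1 asks whether tailored brochures are seen as more useful, but Table 3 covers usefulness only by an indirect yes/no question, while the aim's other two attributes have five-point ratings.

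*Protocol article*

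**What the plan says.** The aims are listed in the introduction, under the heading for the TTCYB intervention. The first is "to determine whether tailored materials are perceived as more useful, understandable, and complete compared to non-tailored ones". It names three attributes and one contrast, tailored against non-tailored.

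Section 2.6.3 says how the judgments are collected. Patients in those two groups are telephoned about seven days after the material is sent, and again after the six-month mailing. The section refers to Table 3 for the detail of the questions. On the five-point scale, Table 3 includes "The material was easy to understand" and "The material was complete". The only question containing the word useful is in the yes/no column: "Do you think it would be useful to receive this kind of material again in the future".

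Section 2.9 gives the analysis of the judgments in one sentence: a t-test, and a "Cross-table with chi-square statistic will be performed". The Discussion says that the efficacy of the tailored intervention "will be evaluated through patients’ judgments about the materials", among other measures. Section 2.6.1 makes change in the four lifestyle behaviours the primary outcome.

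**The concern.** The aim and the questionnaire do not line up on one attribute, and it is the one the aim names first. Patients can grade how understandable and how complete the brochure was. They are never asked to grade how useful it was.

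The statement at stake is that patients found tailored material more useful. As things stand it would rest on the share of patients who would welcome further mailings. The gap cannot be repaired at the analysis stage: once the calls are over, the rating cannot be recovered.

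**Working it through.** The documents give no figure for Aim 1 to reproduce, so the check sets the aim against the questionnaire.

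**Inputs.** The three attributes come from the list of aims, the questions from Table 3, the number of survey rounds from Section 2.6.3 and the tests from Section 2.9. Section 2.9 does not assign tests to items; the last column below assumes the natural pairing of t-test with five-point items and chi-square with yes/no items.

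| Attribute in Aim 1 | Question in Table 3 | Format | What is rated | Test that fits |
|---|---|---|---|---|
| Understandable | "The material was easy to understand" | five-point | the brochure received | t-test |
| Complete | "The material was complete" | five-point | the brochure received | t-test |
| Useful | "Do you think it would be useful to receive this kind of material again in the future" | yes/no | further material of this kind | chi-square |

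The third row differs from the other two in two ways.

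1. *What is asked.* A patient may have found the brochure very useful and still answer no, because it told them what they needed. Another may have found it of little use and answer yes, hoping for something better. The context also changes between rounds. At the first call a second mailing is still to come under Section 2.1. At the second call none is planned. The same answer need not mean the same thing in both rounds.
2. *How finely it is asked.* The aim is comparative: more useful in one group than in the other. A yes/no answer cannot separate a patient who found the material somewhat useful from one who found it very useful. If most patients in both groups say yes, the comparison has little room to show a difference. The documents give no expected proportions, so how far this would matter is unknown.

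**Count.** Two of the three attributes have a direct rating of the brochure received; one has a proxy. With a usefulness rating added, there would be 3 matching ratings per round, or 3 × 2 = 6 comparisons over both rounds.

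**The case against.** The strongest reply is that usefulness is measured, only less directly. The two groups receive different kinds of material, so comparing their answers on whether more of it would be useful does say something about perceived usefulness. Table 3 also rates related matters: whether the material added knowledge, prompted reflection, was pertinent to the patient's situation and might lead to a change in behaviour. In addition, patients complete the measures in Italian (Section 2.3), so Table 3 is probably an English rendering, and fine distinctions of wording should not be pressed too far.

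Much of this stands. It would be wrong to say that usefulness is not asked about at all. But the related items are not tied to the word useful in the aim, and translation is unlikely to account for the difference between rating a brochure and saying yes or no to a further one.

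Two stronger readings are tempting and are not supported.

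- A reader might infer that Aim 1 would be decided over the whole survey without adjustment. Table 3 has 7 single five-point items, one asked for 4 behaviours and 6 yes/no items: 7 + 4 + 6 = 17, or 34 over two rounds. Section 2.9 does not say that all of them decide the aim, and an item such as "Have you read the material" plainly does not bear on it. The matching attributes give 3 tests in one round or 6 in two. At 0.05 each, and if independent, the chance of at least one false positive is 1 − 0.95³ = 0.14 or 1 − 0.95⁶ = 0.265. Even that presumes that any one success would count. The aim joins the three attributes with *and*; if all must be met, no adjustment is needed. Which item and round decide, and with what adjustment, is commonly left to an analysis plan, which is not shown here.
- A reader might infer that Aim 1 cannot be answered. That is too broad, since two of its three attributes have direct ratings.

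**Conclusion.** The mismatch is real and narrow. One of the three attributes in Aim 1 is measured only by an indirect yes/no question, so the finding on usefulness would be weaker than the aim implies. The comparisons of understandability and completeness stand, and the primary outcome and the sample size are untouched. No claim about multiplicity follows from the documents.

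The conclusion assumes that Table 3 reproduces the questionnaire in full, as Section 2.6.3 suggests, and that its English wording is faithful to the Italian. It does not depend on what an analysis plan may say, because such a plan can choose among answers but cannot add a question. Severity: minor; a cheap improvement.

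**What to change.** Add one five-point item, *The material was useful?*, to the judgment calls after both mailings. State in Section 2.9 that the Aim 1 comparison of tailored with non-tailored material uses the three matching ratings: useful, easy to understand and complete. The existing yes/no question can stay as a supplementary item.

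If calls have already begun, reword Aim 1 instead, so that it refers to whether patients would find it useful to be sent such material again.

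The cost is one extra question in calls that are already planned, plus a sentence in Section 2.9.

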## 2. Materials and Methods 

### 2.1. Design

The TTCYB study is a three-arm, parallel-group, randomized intervention designed to determine the effect of tailored print materials for patients with CVDs (see Figure 1). Follow-up assessments will occur at six and 12 months post-baseline evaluation.

At baseline and the six-month follow-up, patients will complete a series of self-report questionnaires evaluating lifestyle behavior, socio-demographic, and psychological characteristics. At the 12-month follow-up, patients will have a telephone interview that will assess lifestyle habits. After the baseline measurement, patients will be randomized into one of three groups: (1) the tailored group, which will receive tailored health brochures; (2) the “non-tailored” group, which will receive non-tailored health brochures; and (3) the usual care group, which will receive no print information materials. Participants will be assigned to one of the three study groups using a stratified randomization process characterized by the unpredictability of assignments. Patients in the tailored and non-tailored group will be mailed a health brochure after a baseline and a six-month evaluation. Within ten working days of completing the questionnaire, both at baseline and the six-month follow-up, the tailored (T) and non-tailored (NT) group will be mailed printed health materials while patients in the usual care (UC) group will receive no materials. Following the delivery of the materials, patients in the T and NT group will be contacted by phone for an interview to measure their judgment of the material. At the 12-month follow-up, all patients will have a telephone interview that will assess their lifestyle in terms of dietary behavior, physical activity, alcohol intake, and smoking behavior.

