### 2.7. Sample Size Estimation

The power analysis was conducted in G*Power (G*Power, Brunsbüttel, Germany) on a repeated-measures ANOVA with within-between interaction with three measurements, three groups, with a correlation among repeated measures about 0.5, a power of 0.80, an alpha level of 0.05, and a small effect size (f = 0.10) [52]. The required sample size was found to be a minimum of 204 patients.

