### 2.8. Data Collection Methods and Data Management

Each center’s personnel will be trained centrally in the study requirements, standardized measurement and the eliciting of information from study participants in a uniform reproducible manner. All data will be entered electronically at the Coordinating Center (University of Milan Bicocca). Original study forms will be entered and kept on file at the Coordinating Center. All forms, files, and datasets related to study data will be kept in locked cabinets. Access to the study data will be restricted. A password system will be utilized to control access; these passwords will be changed regularly. All reports prepared by study group members will be prepared such that no individual subject can be identified.

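### Randomisation is stratified but the stated covariates are only the baseline endpoint values, so linear-model tests will be mildly conservative to the extent that the strata predict follow-up beyond baseline

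*Protocol article*

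**What the plan says.** Section 2.1 of the protocol article describes the allocation: "Participants will be assigned to one of the three study groups using a stratified randomization process characterized by the unpredictability of assignments". It does not name the stratification factors.

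Section 2.9 says that group differences in behaviour and in BMI and blood pressure "will be tested with a repeated-measures ANOVA and logistic and linear regression as appropriate", and gives the adjustment as "using the baseline values of these endpoints as covariates". Other patient characteristics enter only as moderators: "Regressions will also be used to test for interactions of type of material with factors such as self, efficacy, locus of control, age, gender". Nothing in the section puts the stratification factors into a model, and nothing rules them out.

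Section 2.7 sizes the trial on a "repeated-measures ANOVA with within-between interaction with three measurements, three groups", with "a correlation among repeated measures about 0.5", f = 0.10, alpha 0.05 and power 0.80, giving at least 204 patients. Section 2.8 indicates more than one centre ("Each center’s personnel will be trained centrally in the study requirements"), and section 2.3 admits two diagnoses, essential hypertension and ACS. Neither section says that centre or diagnosis is a stratum.

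**The concern.** Stratified allocation makes the arms more alike on the strata than simple randomisation would, so the treatment estimate varies less from trial to trial. A linear model without the strata cannot see this. It leaves the between-stratum variation in its error term and reports a standard error that is too large for the design actually used. The test then rejects less often than its nominal level and intervals are wider than they need be.

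What is at stake is efficiency. The planned 204 patients give power of only 0.806 for the overall test, so there is little margin for avoidable conservatism, and removing it needs no new data.

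**Working it through.** **1. The plan's own figure.** Inputs from section 2.7: k = 3 groups, m = 3 measurements, ρ = 0.5, f = 0.10, alpha 0.05. Sphericity is assumed.

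- λ = f²·N·m/(1−ρ) = 0.01 × 204 × 3/0.5 = 12.24
- df1 = (k−1)(m−1) = 4; df2 = (N−k)(m−1) = 402
- Power is 0.806 at N = 204 and 0.799 at N = 201. The smallest N is 202, or 204 as a multiple of three.

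The stated 204 reproduces. The formula has no term for strata, so it counts on no gain from them.

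**2. Size of the effect in a linear model.** Let R² be the share of residual variance, given the baseline value, that the strata explain. The article gives no such figure, so a range including zero is used. The reference is a single contrast with 80% power when strata are in the model (1.960 + 0.842 = 2.802).

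- Reported over true SE = 1/√(1−R²)
- Actual size = 2·[1 − Φ(1.96/√(1−R²))]
- Power = Φ(2.802 − 1.96/√(1−R²))
- N restoring 80% power = 204 × [(1.96/√(1−R²) + 0.842)/2.802]²

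| Assumed R² | SE too large by | Actual size | Power | N restoring 80% | Extra patients |
|---|---|---|---|---|---|
| 0 | 0% | 0.050 | 0.800 | 204 | 0 |
| 0.05 | 2.6% | 0.044 | 0.785 | 212 | 8 |
| 0.10 | 5.4% | 0.039 | 0.769 | 220 | 16 |
| 0.20 | 11.8% | 0.028 | 0.729 | 239 | 35 |

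Example at R² = 0.10: 1.96/0.9487 = 2.066; (2.066 + 0.842)/2.802 = 1.038; 204 × 1.038² ≈ 220.

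**3. When the effect appears.** A simulation used 204 patients, three arms, four strata, blocks of six, correlation 0.5 and 4000 runs per scenario. The strata and blocks are assumptions. The entries are the mean reported SE without strata divided by that with strata, for the 12-month result.

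| Variance added by or due to strata | Baseline as covariate, strata constant over time | Change from baseline, strata constant over time | Baseline as covariate, strata affect follow-up only | Change from baseline, strata affect follow-up only |
|---|---|---|---|---|
| 0.02 | 0.1487/0.1482 = 1.003 | 0.1711/0.1712 = 1.00 | 0.1508/0.1488 = 1.013 | 0.1730/0.1713 = 1.010 |
| 0.05 | 0.1487/0.1474 = 1.009 | 0.1713/0.1713 = 1.00 | 0.1535/0.1485 = 1.034 | 0.1754/0.1711 = 1.025 |
| 0.10 | 0.1486/0.1459 = 1.019 | 0.1712/0.1712 = 1.00 | 0.1586/0.1490 = 1.064 | 0.1798/0.1714 = 1.049 |
| 0.20 | 0.1487/0.1424 = 1.044 | 0.1713/0.1713 = 1.00 | 0.1676/0.1487 = 1.127 | 0.1878/0.1713 = 1.096 |

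The change from baseline is the kind of within-patient contrast behind the group-by-time test. There, a stratum effect that is the same at every visit cancels exactly. With baseline as a covariate it is largely but not wholly absorbed. The losses in step 2 arise mainly when the strata predict follow-up and not baseline. In that case, with baseline as covariate, rejection under the null was 0.046, 0.038, 0.040 and 0.028 (simulation error about √(0.05 × 0.95/4000) = 0.003).

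**4. True spread of the estimate.** At 0.20 with strata affecting follow-up only, the empirical standard deviation was 0.1496 without strata in the model and 0.1490 with them. Stratified allocation has already delivered the precision. What the omission loses is the correct, smaller reported SE.

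**The case against.** The strongest reply is that section 2.9 is one condensed paragraph of a journal article. It does not say that baseline is the only covariate, and a full analysis plan may add the strata. That limits how firmly the point can be put. It does not remove it, because the article states a covariate set for these comparisons and that set does not match the allocation it describes.

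Four stronger readings are tempting, and the document does not support them.

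- *The standard errors are too large as a matter of fact.* The strata are not named, so their prognostic value beyond baseline is unknown and may be zero. Diagnosis and centre are plausible strata, but the article does not say they are used.
- *The loss is 204/(1−R²) − 204, or about 11, 23 and 51 patients at R² of 5, 10 and 20%.* That formula treats the unadjusted estimate as truly more variable. Stratification has already removed that variance (step 4), so the cost comes only through the conservative test: about 8, 16 and 35.
- *The test that sizes the trial is affected in the same way.* Section 2.7 powers the group-by-time interaction, where constant stratum effects cancel. Only a stratum-by-time effect costs precision there.
- *All planned models report inflated standard errors.* In logistic regression, omitting a prognostic factor pulls the odds ratio towards 1, and adding it usually raises the standard error. Power is still lost, by a different route.

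**Conclusion.** The point holds as a conditional one about efficiency. Stratified allocation is stated, and the covariates stated for the group comparisons are only the baseline endpoint values. If the strata predict follow-up beyond baseline, the linear-model tests are mildly conservative. At an incremental R² of 5 to 10%, the reported SE is 2.6 to 5.4% too large and power falls from 0.80 to 0.785 or 0.769. At 20% the figures are 11.8% and 0.729, and at zero nothing is lost.

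These figures rest on an assumed R², equal allocation, effective balance within strata and a single contrast with 80% power. A reader might infer that the trial's conclusions or its sample size are in doubt. They are not: the error is on the conservative side, and 204 was derived without any credit for stratification.

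**What to change.** Add to section 2.9, or to the analysis plan behind it: *The repeated-measures ANOVA and the linear and logistic regressions for the group comparisons include the factors used to stratify randomisation, together with the baseline value of the endpoint. The repeated-measures model also includes a stratum-by-time term.* List the factors by name there. The stratum-by-time term is needed because a stratum main effect alone does nothing for the group-by-time test.

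The cost is a sentence and a few degrees of freedom. No new data are needed, since stratification factors must be known at randomisation. The article gives neither the number of strata nor the number of centres, and 204 patients over three arms is about 68 per arm. Small strata may therefore need to be pooled in the logistic models, and the pooling rule should be set before the outcome data are seen.
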